## **8. Study Period and Sequences**

### **8.1. Index Procedure**

Consecutive patients undergoing ERCP will be flagged as potentially eligible for study participation. On the day of the procedure, the patient will be approached by a research assistant (RA), who will explain the study, confirm eligibility, and answer any potential questions. If the patient agrees to participate, the relevant informed consent form is signed and witnessed. If the patient decides not to participate, the ERCP proceeds as per the usual standard of care, with or

without the use of DEC as per the endoscopist's discretion (and the sequence that follows does not apply).

1. The RA collects any relevant patient-related and pre-procedural data through combination of direct patient interview and review of the medical records.
2. The patient is randomized to one of the two study arms.
3. The patient enters the endoscopy/fluoroscopy room and the procedure commences.
4. During the ERCP procedure, relevant peri-procedural data are recorded by the RA by direct observation, and/or, if necessary, in consultation with the procedural physician(s) and/or nurse(s).
5. After the procedure is complete, the patient is moved to the recovery room for observation. Depending on their disposition and the course of the procedure, observation times and protocols differ. During this stage, the RA collects any relevant post-procedural data, and any missing pre- or peri-procedural data.
6. Any peri- or immediate post-procedural adverse event(s) is/are recorded.
7. The patient is examined by the endoscopist prior to discharge and provided with written post-procedure information, including a phone number to call in the event of any issues.
8. The RA meets with the patient prior to their discharge from the unit to answer any final potential questions.

## ***8.2. Cleaning and Reprocessing***

After the ERCP is complete, the in-room nursing team will carry out standardized post-endoscopy manual cleaning and disinfection of the DEC or traditional duodenoscope. In cases where the DEC was used, the cap will be disposed of. These processes will be timed by the research assistant. Following this, the scope will be portered to the automated reprocessing room for disinfection and reprocessing, which will also be timed.

## ***8.3. Sampling***

After reprocessing, staff will then observe the following sequence to determine whether there is any persistent bacterial contamination despite standardized disinfection and reprocessing. These samples will then be shipped for microbiologic analysis. The protocol for duodenoscope sampling that will be utilized for this study is adapted from the Duodenoscope Surveillance Sampling and Culturing Protocols, which were developed jointly by the Department

of Health and Human Services, Food and Drug Administration (FDA), Centers for Disease Control and Prevention (CDC), and American Society for Microbiology (ASM). The procedure is summarized here.

1. Two staff are needed to conduct sampling from duodenoscope channels; one person (the sampler) will maintain aseptic handling and conduct brushing steps, while the second person (the facilitator) will open packages and handle the unsampled portions of the duodenoscope.
2. The staff will label the sterile sample containers with relevant information.
3. The staff will don their personal protective equipment (PPE).
4. The staff will set the duodenoscope on a sterile drape.
5. Two samples will be collected and combined. First, an instrument channel sample (from the biopsy port to the distal scope end) will be taken.
6. Second, an elevator recess sample will be taken by flushing and brushing of the elevator recess (in the case of the disposable cap, the distal scope tip to which the disposable cap attaches will be sampled instead, ensuring sampling of the joint line between cap and scope).
7. The duodenoscope will then be handled and transported back to the endoscopy unit according to our local institutional policies.
8. Samples will be packed in appropriate biohazard containers, packaged, and transported for microbiologic analysis. The samples will be assigned a unique study number so that the microbiologic analysts will be blinded to the type of duodenoscope that was used for the index procedure.

#### **8.4. Microbiologic Analysis**

The presence of any microbial population(s) will be assessed using plating for growth in aerobic conditions. 0.1 mL of wash fluid will be plated to blood agar, MacConkey agar, and Columbia blood agar with colistin-nalidixic acid. Growth will be reported in colony-forming units (CFU)/mL. If after 72 hours there is no growth, the sample will be deemed negative, and will be discarded. Positive samples will be further characterized. For Gram-negative bacilli (GNB), these will be reported with CFU/mL and the isolated organism(s) will be reported as identified by matrix-

assisted laser desorption/ionization (MALDI). Non-GNB organisms will be reported with CFU/mL and a group identification (ie, coagulase-negative *Staphylococcus*, or *Candida*).

### **8.5. Follow-up**

Patients will be contacted by the RA by telephone 30 days following their ERCP to assess for any ongoing symptoms and advise of any adverse events, including unplanned emergency department visits or inpatient admissions. The patient's medical record is also reviewed at 30 days for complete details of any unplanned emergency department visits, inpatient admissions or prolonged admissions.

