### **5.4. Randomization and Allocation**

Patients fulfilling the inclusion/exclusion criteria above will be randomized following consent in a 1:1 ratio. Permuted block randomization will be utilized in blocks of 8 patients. Allocation will be to one of two groups: 1) ERCP using ED34-i10T2 duodenoscope with DEC or 2) ERCP using a conventional duodenoscope (ED34-i10T). Confidential random number allocation will be accessed via a secure internet software. The study investigators, outcome adjudicators and patients will be blinded to allocation. The endoscopist will not be blinded. In cases where additional or alternate duodenoscope(s) is/are required to achieve the desired goal of the ERCP procedure, the choice(s) of device(s) will be left to the discretion of the endoscopist, regardless of the study arm to which the patient has been allocated.

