## **6. Data Management**

### **6.1. Data Sources**

The investigators have previously designed and implemented the Calgary Registry for Advanced and Therapeutic Endoscopy (CReATE, University of Calgary Conjoint Health Research Ethics Board 18-0410). CReATE is a high-fidelity prospective database that seeks to answer questions in ERCP outcomes research. As such, over 400 data fields are collected in real-time for each ERCP procedure, including detailed patient-, endoscopist- and procedure-based

variables. Therefore, CReATE serves as the ideal data collection platform for this randomized trial.

Data are inputted by a full-time research assistant, and stored and managed on a secure web application specializing in healthcare database implementation and maintenance, REDCap. This web portal allows for facile access to secure data. The web portal is secured by the latest security technology. Study participants will be identifiable on the secure platform for purposes of patient contact, follow-up and potential withdrawal. For the purposes of this randomized study, an additional tab will be created in the electronic interface that will allow for entry of the arm to which the patient has been randomized. Whenever data are exported for analysis, they will be de-identified and assigned unique study codes only. The primary investigator will be the custodian of the identifiable electronic data, which will be stored only on a secure server accessible only via combination of password protection and temporary electronic fob.

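### The 30-day harms call is made by a research assistant whose other tasks reveal the arm, and no blinded step is described for the harms and clinical-success outcomes that need judgement

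*Supplement*

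**What the plan says.** All references are to the latest (two-site) protocol and to the SAP.

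- **Blinding, section 5.4.** "The study investigators, outcome adjudicators and patients will be blinded to allocation", followed by "The endoscopist will not be blinded". The research assistant (RA) is in neither group.
- **Procedure, section 8.1, step 4.** During the ERCP "relevant peri-procedural data are recorded by the RA by direct observation", with the procedural staff consulted where needed.
- **Cleaning, section 8.2.** "In cases where the DEC was used, the cap will be disposed of", and "These processes will be timed by the research assistant".
- **Database, section 6.1.** "Data are inputted by a full-time research assistant". For this trial "an additional tab will be created in the electronic interface that will allow for entry of the arm". Who fills in or can view that tab is not stated.
- **Follow-up, section 8.5.** "Patients will be contacted by the RA by telephone 30 days following their ERCP to assess for any ongoing symptoms"; the call also covers adverse events. The medical record is reviewed at 30 days as well, for emergency visits and admissions, but the reviewer is not named.
- **Adjudication, section 7.1.** Two blinded adjudicators, with a third for disagreements, judge technical success from redacted reports. Section 8.3 blinds the microbiology analysts. Section 7.2 names no assessor for adverse events or clinical success.
- **SAP, sections A to C.** Safety and secondary outcomes are analysed in 518 patients. Pancreatitis, bleeding, perforation, cholangitis, cardiorespiratory events and death are each described as obtained at 30-day follow-up. Arms are compared unadjusted, by relative risk and number needed to treat with 95% confidence intervals.

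**The concern.** Both co-primary outcomes have a blinded reader between the procedure and the analysis. The 30-day harms and clinical success have none that is described, and the person who elicits symptoms holds a role that knows which scope was used.

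Knowledge of the arm can act at three points: how hard the caller probes, whether a complaint is recorded as an event, and how the event is graded or attributed. Harms after ERCP are probably few in each arm, so a handful of soft decisions could move a relative risk. A device trial that hopes to report similar safety alongside non-inferior technical success would want that comparison to be as well protected as its primary outcomes.

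There is also a reporting problem. A reader of 5.4 sees blinded outcome adjudicators and one unblinded party, the endoscopist, and may reasonably assume that safety was assessed blind.

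**Working it through.** The plan states no figure that could be reproduced here. The check is a trace of one role through the protocol, then a sort of the outcomes by how much judgement they need.

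**Step 1. Does the RA role know the arm?** Direct observation of the ERCP (8.1) and timing of a cleaning process that includes cap disposal in one arm only (8.2) each reveal it. The arm tab (6.1) is weaker evidence, because access to it is not described. The first two are enough.

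**Step 2. Does that role ascertain outcomes?** Yes, for the 30-day telephone assessment (8.5). Nothing requires a different or blinded caller, and no call script is described. The record review in the same section is a second source, with its reviewer and blinding unstated.

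**Step 3. Is there a later blinded step?** For technical success, yes (7.1). For microbiology, yes (8.3). For 30-day harms and clinical success, none is described. The A/B coding of the arm in SAP section B masks the analyst, not the assessor.

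**Step 4. Which outcomes are exposed?** Sorting the section 7.2 list:

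| Outcome | Objective part | Part needing judgement |
|---|---|---|
| Pancreatitis | Lipase more than three times the upper limit | Whether the pain is new or different |
| Bleeding | Haemoglobin drop | Reported visible bleeding |
| Cholangitis or sepsis | None written in 7.2 | The whole classification |
| Overall adverse events | ASGE Lexicon definitions | Applying them; severity grade |
| Clinical success | Return visit or admission on record | Whether the return is tied to persisting disease |
| Admission or acute-care visit | On record | Little |
| Death | On record | Very little |

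**Step 5. What would blinded classification cost?** The input from the documents is 518 patients (SAP section A). The share with any possible event is not given; I assume 10 to 15%.

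- 518 × 0.10 = 51.8, about 52 records
- 518 × 0.15 = 77.7, about 78 records

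**The case against.** The strongest reply has four parts.

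1. **5.4 is not contradicted.** It never lists the RA as blinded and never says that the safety comparison is blinded. This stands. A reader might infer that the protocol breaks its own blinding statement; the text supports only that it is silent on this role.

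2. **The RA is not the only source.** A reader might infer that every 30-day harm comes from one unblinded person. The record review can pick up visits and admissions independently of the call, and its reviewer is not named. The RA is also a role: with two sites, the individual who watched may not be the one who calls. Both points stand, but the protocol requires neither a separate caller nor a blinded record reviewer.

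3. **Many outcomes are hard to bend, and patients are blinded.** Pancreatitis needs a lipase criterion as well as pain, bleeding has a haemoglobin criterion, and death and admissions are on record. Patient blinding limits bias in what is reported. This narrows the exposure to the judgement items in Step 4. It does not remove probing, grading or attribution by someone who knows the arm.

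4. **No direction or size can be shown.** Section 3.2 mentions more than 50 informal cases with the new device and no problems, and a reader might infer under-recording in that arm. That remark says nothing about how an RA questions patients. An invented example does not help. Take 259 per arm (518 / 2) and an assumed 10% event rate, so 26 v 26. Losing one event in five in one arm gives 21 v 26, a relative risk of 21/26 = 0.81 with a 95% interval of about 0.47 to 1.40. The result merely returns the assumed loss, and no safety hypothesis or margin is specified that it could overturn. This part stands in full.

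**Conclusion.** The gap is real and limited. A role that the protocol's own procedures unblind makes the 30-day assessment, and no blinded step is described for the judgement-dependent secondary outcomes: the pain component of pancreatitis, cholangitis or sepsis, severity grading, and the relatedness of return visits in clinical success. Section 5.4 omits this and may mislead by what it leaves out.

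The co-primary outcomes are not affected by this point. The documents do not support any claim about which arm would be favoured or by how much. The conclusion rests on reading the RA as one role throughout, with no separation of tasks, as the protocol is written. If the sites do use a separate blinded caller or record reviewer, the protocol need only say so. This is a worthwhile, inexpensive improvement to secondary outcomes, not a threat to the main result.

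**What to change.** 1. **Adjudicate.** Have the two blinded adjudicators already appointed for technical success, with the third for disagreements, classify each possible 30-day event and clinical success from redacted call notes and records, using the section 7.2 and ASGE definitions. Redaction should remove scope model and any mention of the cap. Send a record forward on any positive answer in the call or any recorded visit or admission, so that the unblinded caller does not do the filtering.
2. **Analyse that classification.** State in SAP section B that the adverse event variables, and clinical success, are the adjudicated ones.
3. **Use a fixed call script**, identical in both arms. If calls are already complete, this step is no longer available, but steps 1 and 2 still are.
4. **At a minimum**, add a sentence to 5.4 stating that 30-day harms are ascertained by staff who are not blinded to the arm.

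The cost is protocol and SAP wording plus redaction and adjudicator time for about 52 to 78 records, under the assumed 10 to 15%. No new staff or patient procedure is needed. Adjudication cannot recover an event that was never elicited or recorded, so the call script is part of the remedy.

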### **8.5. Participant Withdrawal**

In accordance with the Declaration of Helsinki and the International Conference on Harmonisation of Technical Requirements for Registration of Pharmaceuticals for Human Use Good Practice Guidelines, a participant is free to withdraw from participation in the study at any time, for any reason without prejudice to their future medical care by the physician or the institution. The investigator(s) may also withdraw the participant at any time in the interests of patient safety. Participants may be removed from the study if one or more of the following events occur:

- withdrawal of consent;
- decision is made by the investigator(s) that removal from the study is in the patient's best medical interest;
- study is stopped by ethics/regulatory authorities.

If a subject withdraws from the clinical investigation, the primary or any additional reason(s) shall be reported. All applicable case report forms up to the point of subject withdrawal, including an End of Study form, should be completed.

Subjects who are "lost-to-follow-up" will have three documented attempts to contact them prior to completion of the End of Study form. If withdrawal is due to investigator's discretion, the investigator should describe what follow-up activities the investigator shall perform. Unless the withdrawal is due to a Serious Adverse Event (SAE), additional subject data will not be collected after the point at which the subject has been withdrawn or withdraws consent from the study. Data collected up to the point of withdrawal may be used by the investigators as permitted in the Informed Consent Form (ICF).

## **8.6. End-of-Study Definition**

This clinical trial will be considered complete when participants are no longer being examined or the last participant's final 30-day follow-up check has occurred. A participant will be considered to have completed the study if he or she has completed the index procedure in addition to the follow-up phone assessment at the 30-day timepoint.

## **9. Statistical Considerations**

### **9.1. Hypothesis and Sample Size Calculations**

The first co-primary outcome considers technical success of the ERCP procedure. Overall technical success rates in ERCP vary widely depending on the definitions employed. It is widely agreed upon that a cannulation rate greater than 90% (in native papillae) is an attainable key performance indicator (KPI) in ERCP performed for choledocholithiasis. However, in cases of malignant biliary obstruction, especially at low-volume centers, cannulation rates appear to be significantly lower. When one considers overall procedural success rate, these targets become even less clear, with studies reporting between 60 and 90% success rates depending on the definitions employed.

Prospective data from our center have been analyzed to assess our group's rates, based on 10 months of procedures in over 600 patients having undergone ERCP. Deep cannulation rates in native papillae at our center are approximately 96%. Overall procedural success in all-comers is approximately 92%, with 4% representing cannulation failures, 4% representing inability to clear or relieve obstruction in the duct(s) of interest.

Thus, when comparing clinical efficacy between DEC and traditional duodenoscopes, we selected an overall baseline technical success rate of 92% based on our experience. We propose that technical success of DEC within a margin of 7% of traditional duodenoscopes will result in an ability to conclude non-inferiority of DEC. A hypothesis will therefore be tested that the overall technical success rate with DEC will be at least 85%:

$$H_0: P_{CON} \geq P_{DEC} + d \text{ (Inferior)} \quad H_1: P_{CON} - d < P_{DEC} \text{ (Non-inferior)}$$

where  $P_{DEC}$  is the overall technical success rate for DEC in this study,  $P_{CON}$  is the overall technical success rate for traditionally designed duodenoscopes (control),  $d$  is the set non-inferiority limit of 7%, and  $H_0$  and  $H_1$  are the null and alternate hypotheses, respectively.

An exact test will be used to test the one-sided hypothesis that DEC is non-inferior to control duodenoscopes. Using a power of 80% with a one-sided alpha of 0.025, 236 subjects in each arm will be required, for a total of 472 patients. To compensate for possible loss of subjects due to attrition, an additional 10% of subjects will be enrolled, for a **total of 520 subjects**. It is therefore estimated that the study will require **9-12 months to complete**, based on the estimated volume of ERCPs and study enrolment rates at our center. No interim analyses will be planned.

The second co-primary outcome considers persistent bacterial contamination rate of the duodenoscopes after ERCP. A recent nation-wide analysis showed a persistent bacterial contamination rate of 22% after standard disinfection and reprocessing of duodenoscopes. This was common across multiple duodenoscope manufacturers and models. In particular, the Pentax ED34-i10T duodenoscope demonstrated a persistent contamination rate of 27%, though there was a small sample size of 11 assessing this group. No other published studies have reported specifically on reprocessing of ED34-i10T. However, real-world data from the FDA demonstrate a 9.3% total sample positivity rate among Pentax duodenoscopes. Furthermore, our preliminary data based on post-reprocessing bioluminescence scans demonstrate that 10% of ED34-i10T duodenoscopes require repeat re-processing due to counts representative of residual contamination.

Thus, when comparing persistent contamination between DEC and traditional duodenoscopes, we set an overall expected persistent contamination rate of 10% in the control arm. We propose that reduction in persistent bacterial contamination from 10% with ED34-i10T to 3% with DEC (a relative risk reduction of 67%) would be considered clinically significant. A hypothesis will therefore be tested that the persistent bacterial colonization rate with DEC will be 3% or lower:

$$H_0: P_{DEC} \geq P_{CON} \text{ (Equivalent or Inferior)} \quad H_1: P_{DEC} < P_{CON} \text{ (Superior)}$$

where  $P_{DEC}$  is the persistent contamination rate for DEC in this study,  $P_{CON}$  is the persistent contamination rate for traditionally designed duodenoscopes (control), and  $H_0$  and  $H_1$  are the null and alternate hypotheses, respectively.

An exact test will be used to test the two-sided hypothesis that DEC is superior to control duodenoscopes in terms of persistent bacterial contamination. Using a power of 80% with a two-sided alpha of 0.05, 194 subjects in each arm will be required, for a total of 388 patients. To compensate for possible errors in sampling or loss of samples through transportation, an additional 10% of duodenoscopes will be sampled, for a **total of 426 subjects**. For the purposes

of the second co-primary objective of the study, the first 426 patients enrolled as part of the first co-primary objective will have their duodenoscopes sampled (213 from each arm). An anticipated 25% of the sample size will be recruited from Kingston.

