### C) ANALYSIS

Two-tailed Fisher's exact tests and chi-squared tests will be used to compare proportions. Outcomes will be compared between groups in an intention-to-treat analysis without adjustment. Comparisons will be reported using relative risks (RRs) and numbers needed to treat (NNTs) along with their respective 95% confidence intervals (CIs).

*Post hoc* subgroup analyses will be performed on sex (female or male), age (<65 or ≥65 years), study site (Calgary or Kingston), procedural complexity (1-2 or 3-4), papilla status (native

papilla or prior sphincterotomy), disposition (inpatient or outpatient), biliary stent placement (present or none), and indication (suspected or confirmed malignancy or all others). All statistical analyses will be performed using RStudio version 1.2.1335 (Integrated Development Environment for R, Boston, USA).

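### The 194 and 236 per arm in section 9.1 come from large-sample formulas, not exact tests; Fisher's test at 194 per arm has 76.5% power, and 10% to 3% is a 70% reduction, not 67% (minor)

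*Supplement*

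**What the plan says.** Section 9.1 of the latest protocol version sizes two co-primary outcomes, and promises an exact test for each.

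- **Contamination (superiority).** "An exact test will be used to test the two-sided hypothesis that DEC is superior to control duodenoscopes" on persistent contamination. The design effect is a "reduction in persistent bacterial contamination from 10% with ED34-i10T to 3% with DEC (a relative risk reduction of 67"%). The size follows: "Using a power of 80% with a two-sided alpha of 0.05, 194 subjects in each arm will be required". A 10% addition for sampling errors and lost samples brings the total to 426, and the first 426 patients "will have their duodenoscopes sampled (213 from each arm").
- **Technical success (non-inferiority).** The protocol states "we selected an overall baseline technical success rate of 92% based on our experience", a margin of 7 percentage points, one-sided alpha of 0.025 and 80% power. From these, "236 subjects in each arm will be required, for a total of 472 patients", raised by 10% for attrition to 520.

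The protocol does not say which exact test is meant in either case. SAP section C says: "Two-tailed Fisher's exact tests and chi-squared tests will be used to compare proportions". It assigns neither test to a particular outcome and does not say whether the chi-squared test is continuity-corrected. SAP section A gives N = 422 for microbiology and N = 518 for technical success.

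**The concern.** Exact tests are usually more conservative than the large-sample formulas used to size two-proportion comparisons, most noticeably when event rates are low, as with 3% and 10% here. If the sizes come from large-sample formulas and the analysis uses Fisher's test, the stated 80% is not what the planned analysis delivers, and the 10% meant to cover lost samples is partly spent on reaching 80%.

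Two further points sit in the same text. The relative reduction that defines the clinically important effect does not agree with the two rates beside it. And the SAP leaves two candidate tests for a co-primary outcome. If they can disagree at 0.05, the confirmatory one should be fixed before the data are seen.

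**Working it through.** **Inputs.** From section 9.1: contamination 10% versus 3%, two-sided alpha 0.05, 80% power, 194 per arm (213 after inflation); technical success 92% (taken as the true rate in both arms), margin 7 points, one-sided alpha 0.025, 80% power, 236 per arm (260 after inflation). From SAP section A: N = 422 and 518, taken as 211 and 259 per arm. Independent observations are assumed throughout.

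**1. Reproducing 194.** The pooled large-sample formula without continuity correction, with mean rate 0.065:

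n = [1.96 × √(2 × 0.065 × 0.935) + 0.8416 × √(0.10 × 0.90 + 0.03 × 0.97)]² / 0.07² = [0.6833 + 0.2904]² / 0.0049 = 193.5, so 194.

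**2. Reproducing 236.** The normal-approximation non-inferiority formula:

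n = (1.96 + 0.8416)² × 2 × 0.92 × 0.08 / 0.07² = 235.8, so 236.

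Both planned sizes are therefore large-sample figures.

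**3. Power for contamination.** Every pair of binomial counts was enumerated at 10% and 3%, and the probabilities of those with two-sided p ≤ 0.05 were summed:

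| Per arm | Fisher | Chi-squared, uncorrected |
|---|---|---|
| 194 | 76.5% | 82.4% |
| 208 | 79.9% | 84.5% |
| 209 | 80.1% | 84.7% |
| 211 (SAP 422) | 80.6% | 85.1% |
| 213 (protocol 426) | 81.0% | 85.4% |

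Fisher first reaches 80% at 209 per arm. The inflation adds 213 − 194 = 19 per arm, and reaching 80% takes 209 − 194 = 15 of those, leaving 4 for actual losses.

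Other exact tests at 194 per arm: Boschloo about 79.5%, a Barnard-type unconditional test 81.8%.

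**4. Power for technical success.** No document specifies the exact non-inferiority test, so one has to be assumed. An unconditional exact test ordered by the Farrington-Manning score, with its size held at 0.025 over the nuisance rate, gives 76.9% at 236 per arm, 80.2% at 252, 81.4% at 259 and 81.2% at 260. Ordering by the unpooled Z statistic instead gives 60.4% at 236.

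**5. Relative reduction.** (10 − 3)/10 = 70%. A 67% reduction would mean 3.3% with DEC, and the formula in step 1 would then give 215.9, so 216 per arm. The 194 reproduces only with 3%, so the error is in the percentage and not in the sizing.

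**6. Can the two SAP tests disagree?** Take 20/211 versus 9/211. Fisher p = 0.053; uncorrected chi-squared p = 0.034; continuity-corrected chi-squared p = 0.054. At the design rates with 211 per arm, Fisher and the uncorrected chi-squared disagree at 0.05 in about 4.5% of trials.

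**The case against.** The strongest reply has four parts.

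- **The protocol says only that an exact test will be used.** A Barnard-type test is exact and has 81.8% power at 194 per arm, so a reader should not infer that no exact test delivers 80% at the stated size. That is correct, and the 76.5% belongs to Fisher alone. But Fisher is the only exact test either document names, so it is the natural reading until another is specified.
- **The non-inferiority figure depends on a test the reviewer has chosen.** This also stands. It ranges from about 60% to 77% at 236 per arm with the ordering, so it supports asking for the test to be named, and no single figure can be put into the protocol until that is done.
- **The conflict between tests needs the uncorrected chi-squared.** True: the corrected version agrees with Fisher in the example. The protocol also limits the co-primaries to exact tests, and the SAP sentence may be meant to assign chi-squared to its many descriptive variables. The SAP does not say so, however, nor whether a correction applies.
- **The trial is not underpowered in practice.** A reader might infer from 76.5% that it is. The SAP's 422 and 518 give about 80.6% and 81%, so the documents do not support that reading. Nor is type I error at risk from using Fisher, which is conservative.

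**Conclusion.** The point holds, as a minor one. The text contains one unconditional error, 67% where the stated rates give 70%, and one power statement that does not match the named test: 76.5% at 194 per arm under Fisher, against a stated 80%. For non-inferiority the power at 236 per arm cannot be stated until the exact test is specified; with a score-ordered unconditional test it is about 77%.

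At the numbers the SAP lists, power is about 80.6% (Fisher) and about 81% (score-ordered exact non-inferiority test). Under Fisher, most of the sampling-loss allowance, though not all of it, goes to reaching 80%. Had losses used up the whole allowance and left 194 per arm, power would have been 76.5%.

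The unassigned pair of tests in the SAP matters only if the chi-squared is uncorrected and the result is near 0.05. It is simple to close off.

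The conclusion rests on the protocol's design rates, equal arms and independent observations.

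**What to change.** In protocol section 9.1:

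1. State that 194 per arm gives 76.5% power under Fisher's exact test, that 80% needs 209 per arm, and that the inflated sample covers this.
2. Name the exact non-inferiority test and give its power at 236 per arm.
3. Change the relative risk reduction from 67% to 70%.

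In SAP section C, name one exact test as confirmatory for each co-primary outcome, and limit chi-squared tests to the other comparisons of proportions. For contamination, Fisher or an unconditional exact test such as Boschloo's would serve, provided the choice is fixed in advance and the power statement matches it. For technical success, the named test must address the 7-point margin.

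The cost is a few sentences. No extra patients or samples are needed.
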